### Outcome measures

The primary outcome measures are major obstetric haemorrhage (estimated blood loss ≥ 1000 ml) and use of an additional uterotonic agent. Estimated blood loss of ≥1000 ml has been chosen to reflect major obstetric haemorrhage and it is widely accepted that clinicians underestimate rather than overestimate blood loss. This estimate will be based on the difference between pre-operative and post-operative haematocrit (EBL_calc _– Calculated estimated blood loss). [14]

The estimate is calculated as follows:

Where EBV estimated blood volume = Booking weight in kg × 85

Secondary outcomes include mean estimated blood loss (as measured by theatre staff), change in haemoglobin and haematocrit, significant anaemia (Hb fall = 20%) 48 hours after delivery, need for blood transfusion, side effects (including vomiting and hypotension) and length of postnatal stay in theatre/recovery and in hospital. Hypotension will be defined as a fall in blood pressure of more than 30% below the pre-operative blood pressure and/or use of ephedrine.

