Anaesthesia will also be standardised. An intravenous bolus of 500 ml crystalloid should be given to all patients prior to spinal anaesthesia. A size 25G pencil-point needle should be used at a suitable lumbar interspace. The patient can be sitting or in the left lateral position for spinal anaesthesia. The anaesthetic solution will consist of 2 ml 0.5% hypertonic bupivocaine (2.2 ml in the sitting position), 10–20 μg fentanyl and 0.1 mg preservative free morphine. Anaesthesia should be to the level of T5, as assessed by touch. The patient will be tilted 15° to the left of supine and standard monitoring used as per the AAGBI guidelines. The sphygmomanometer cuff should be placed on the left arm. Haemodynamic monitoring will be performed before spinal anaesthesia, every minute until 10 minutes after delivery, every 15 minutes during the first postoperative hour then every 30 minutes for 4 hours. For the purpose of this study, baseline haemodynamic variables will be regarded as those immediately after clamping of the cord and before administration of syntocinon 5 IU. The investigators accept that individual anaesthetists may deviate from this protocol according to clinical needs. This is acceptable and should be documented on the case report form.

Intraoperative hypotension will be treated with intravenous boluses of phenylephrine 50 μg. If the heart rate falls below 60/min, intravenous boluses ephedrine 6 mg will be substituted. The anaesthetist will aim to maintain blood pressure at preoperative values. After delivery, the operating table tilt will be removed and the patient placed in the full supine position. Blood loss at operation will be replaced with colloid infusion or blood as deemed necessary by the anaesthetist. Postoperative pain relief will consist of regular non-steroidal analgesia combined with paracetamol. Opiates in the form of oxynorm can be used with caution considering the use of intrathecal opiates. Again it is acceptable for the local administrator to use any form of analgesia as per local practice and to document it on the case report form.

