### Data monitoring and Ethics Committee (DMEC)

An independent safety and data monitoring committee will also be formed. They will meet yearly to examine recruitment figures, baseline data, retention and adverse events. The DMEC will not undertake any formal interim analyses for either safety or effectiveness and therefore there are no formal stopping rules. There is no evidence of adverse reactions associated with oxytocin infusion. Although adverse reactions have been shown to be associated with the 5 IU oxytocin bolus, all trial participants will receive a bolus, and thus we do not anticipate any differences in rates of adverse events between the groups. However all adverse events will be reported to the DMEC who will report these data to the Trial Steering Committee. Additionally, in the event of a postpartum haemorrhage, clinicians are permitted to discontinue the trial infusion and commence a known 40 IU oxytocin infusion.

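### The hypotension outcome counts ephedrine use but not use of phenylephrine, the pressor named first; its reference pressure conflicts with the stated study baseline; and it has no start time

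*Protocol article*

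**What the plan says.** Hypotension is one of two side effects named among the secondary outcomes (Secondary outcomes; Outcome measures). The definition under Outcome measures is: "Hypotension will be defined as a fall in blood pressure of more than 30% below the pre-operative blood pressure and/or use of ephedrine". It names one pressor and gives no counting window.

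The anaesthesia paragraphs under Intervention say four things that bear on it:

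- Treatment: "Intraoperative hypotension will be treated with intravenous boluses of phenylephrine 50 μg".
- When ephedrine is used: "If the heart rate falls below 60/min, intravenous boluses ephedrine 6 mg will be substituted".
- Reference point, set specifically with the trial in mind: "baseline haemodynamic variables will be regarded as those immediately after clamping of the cord and before administration of syntocinon 5 IU".
- Observation and target: "Haemodynamic monitoring will be performed before spinal anaesthesia, every minute until 10 minutes after delivery", then at wider intervals for some hours after surgery. Also, "The anaesthetist will aim to maintain blood pressure at preoperative values".

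The DMEC section expects no difference in harm: "all trial participants will receive a bolus, and thus we do not anticipate any differences in rates of adverse events between the groups". It plans no formal interim analysis for safety.

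**The concern.** The definition does not fit the conduct described in the preceding section, in three ways.

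1. **Pressor.** Use of ephedrine is an event in itself; use of phenylephrine is not. Under the stated treatment rule, heart rate decides which drug is given, so for smaller falls heart rate decides who is counted.
2. **Reference pressure.** One section measures from the pre-operative value. The other fixes the study baseline after the spinal and after delivery.
3. **Start of counting.** With a pre-operative reference, monitoring from before the spinal and no start time, events before cord clamping qualify as written. Nothing randomised has been given by then.

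What is at stake is a harm comparison. The protocol assumes the infusion adds no adverse events, and the hypotension comparison is one of the planned checks on that assumption. A definition that loses true events and admits unrelated ones makes a finding of no difference less informative.

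**Working it through.** The protocol states no rate, effect or power for hypotension, so there is no figure to reproduce. The first two steps compare text; the last two illustrate size under assumptions.

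**Step 1: which treated women are events.** Apply the definition to the two named pressors.

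| Fall from pre-operative pressure | Phenylephrine only | Ephedrine given |
|---|---|---|
| More than 30% | event | event |
| 30% or less | **non-event** | **event** |

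Only the lower row is inconsistent. It is not an empty category: the anaesthetist aims to hold pressure at pre-operative values, so treatment can come before a 30% fall.

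**Step 2: the two reference pressures.** Assume a pre-operative systolic pressure of 120 and a value of 100 just after cord clamping (neither is in the documents).

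- Threshold from the pre-operative value: 0.7 × 120 = 84.
- Threshold from the cord-clamp value: 0.7 × 100 = 70.
- A pressure of 84 is a fall of 1 − 84/100 = 16% from the stated study baseline.

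Readings between 70 and 84 are events under one reference and not under the other.

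**Step 3: effect of pre-delivery events.** Inputs: 1000 per arm (Sample size section); two-sided 5% test. Assumed: post-clamp hypotension of 5% (placebo) and 10% (infusion), and a pre-delivery share b, equal in both arms and independent of later events. The observed risk is 1 − (1 − b)(1 − p). Power is Φ[(d − 1.96 × SE₀)/SE₁], where SE₀ uses the pooled proportion and SE₁ the separate ones.

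- b = 0: 5% vs 10%. SE₀ = √(0.075 × 0.925 × 2/1000) = 0.01178; SE₁ = √((0.0475 + 0.0900)/1000) = 0.01173. (0.05 − 0.02309)/0.01173 = 2.295, power 98.9%.
- b = 0.2: 1 − 0.8 × 0.95 = 24% vs 1 − 0.8 × 0.90 = 28%. SE₀ = √(0.26 × 0.74 × 2/1000) = 0.01962; SE₁ = √((0.1824 + 0.2016)/1000) = 0.01960. (0.04 − 0.03845)/0.01960 = 0.079, power 53.2%.

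| Assumed b | Observed risks | Risk ratio | Power |
|---|---|---|---|
| 0 | 5% vs 10% | 2.00 | 98.9% |
| 20% | 24% vs 28% | 1.17 | 53.2% |
| 40% | 43% vs 46% | 1.07 | 27.1% |
| 60% | 62% vs 64% | 1.03 | 15.1% |

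With a smaller assumed effect, 5% vs 8%, power is 77.7% at b = 0 and 23.4% at b = 20%.

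**Step 4: effect of missed phenylephrine cases.** Assume half of the true cases are missed in each arm. Then 5% vs 10% becomes 2.5% vs 5%.

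- Odds ratio before: (0.10/0.90)/(0.05/0.95) = 2.11. After: (0.05/0.95)/(0.025/0.975) = 2.05.
- Power before: 98.9%. After: 83.8%.

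Missed cases cost power and absolute difference but hardly move the odds ratio, which is the measure the Statistical analysis section reports.

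**The case against.** The strongest reply is that this is an unpowered secondary outcome in a condensed article, and that several tempting readings go too far. Most of those limits stand:

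- A reader might infer that phenylephrine-treated women are never counted, or that most treated episodes are missed. Any woman whose pressure falls by more than 30% counts whichever drug she receives, and the documents give no rates of pressor use from which to call the loss large.
- A reader might infer that both faults pull the effect estimate towards the null. Only the unrelated pre-delivery events do so; Step 4 shows that missed cases in equal shares do not.
- A reader might infer that the protocol sets out to count spinal hypotension. It never says so. The cord-clamp baseline even suggests assessment from that point. The inclusion follows only from the missing start time, and a counting window might stand in a fuller document.
- A reader might infer bias in favour of one arm. Randomisation makes pre-delivery events equal on average.
- A reader might infer that harm is judged by hypotension and vomiting alone. The side-effect list is not closed, all adverse events go to the DMEC, and serious events are reported separately.
- The pre-operative reference agrees with the stated pressure target, and Step 2 shows that the cord-clamp reference could lower the threshold and count fewer events. The documents do not settle which was meant.

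What the reply does not answer is that the pressor criterion and the reference pressure are stated rules in conflict with other stated rules, not details left to another document.

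**Conclusion.** The point holds for the two explicit mismatches. As written, a treated fall of 30% or less is an event or a non-event according to which pressor was given, and the reference pressure contradicts the study baseline set in the Intervention section. Nothing else in the document resolves either. The admission of events before cord clamping is an inference from the absent start time, but it follows from the wording: the stated baseline places even the common bolus after clamping. The start of the infusion is not given in words; I take it to be no earlier than the bolus.

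The consequence is lost power and, through pre-delivery events, dilution towards no difference in a safety comparison. Its size cannot be taken from the documents. The fall from about 99% to 53% rests on an assumed 10% vs 5%, an assumed 20% pre-delivery share, and independence. Because the outcome is secondary, this should be corrected but does not threaten the trial's main conclusion.

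**What to change.** Leave treatment as it is and change only the outcome definition:

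1. Extend the pressor criterion to use of either vasopressor named in the Intervention section.
2. Count events from cord clamping to the end of the stated monitoring period, and report hypotension before delivery separately.
3. Reconcile the reference pressure between Intervention and Outcome measures. State one for the main analysis and report the other as a sensitivity analysis.

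The cost is small: definition wording, plus a time for each pressor dose on the case report form. Pressure is already recorded every minute until 10 minutes after delivery. One limit remains: hypotension caused by the bolus, which both arms receive, would still be counted, so some dilution would persist.

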### Follow-up

A routine full blood count will be performed 48 hours after delivery to assess haemoglobin and haematocrit. Clinical follow-up of the mother will be completed prior to hospital discharge.

### Trial end

The trial will be considered complete after the final review of the last trial participant. The end of the trial will be notified to the Competent Authority and the Ethics Committee using the appropriate form.

### Statistical analysis

Data analysis and reporting will proceed according to CONSORT guidelines for randomised controlled trials, and will be conducted blinded to group status by the trial statistician and researcher. The first stage of analysis will be to use descriptive statistics to describe recruited individuals in relation to those eligible, and to investigate comparability of the trial arms at baseline. The primary analyses will involve intention-to-treat comparisons between the two groups for the primary outcomes, with transformation as appropriate after examination of distributions, and adjusted for stratification variables. Secondary analyses will investigate the effects of further adjustment for any variables displaying marked imbalance between the arms at baseline. Secondary outcomes will be analysed in a similar way. All analyses will use appropriate (that is, logistic or linear) regression models, with results presented as point estimates (odds ratios or difference in means), 95% confidence intervals and p values. Further secondary analyses will involve planned subgroup analyses and will use multivariable regression models with appropriate interaction terms to ascertain any differential effects in relation to repeat caesarean section, choice of anaesthetic, and operator experience.

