### Secondary outcomes

- to compare the estimated mean operative blood loss between the two groups (as measured by theatre staff)

- to compare early lochial loss following oxytocin bolus compared with oxytocin bolus and infusion

- to compare the objective change in haemoglobin and haematocrit before and 48 hours after delivery between the two groups

- to compare the incidence of severe anaemia (Hb fall ≥ 20%) 48 hours after delivery between the two groups (or patient transfused).

- to compare the need for blood transfusion and/or blood products

- to compare the incidence of side effects (vomiting, hypotension)

- to compare the postnatal length of stay in theatre/recovery and in the hospital

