### Sample size

We estimate from the pilot study that 5–10% of study participants will have an estimated blood loss of > 1000 ml. The rate is around 15% for the calculated estimate (EBL_calc_) and this is more likely to be an accurate reflection of actual blood loss. We found relative reductions of between 20–50% in the outcome measures on comparing infusion and placebo in the pilot study, but with wide 95% confidence intervals around these estimates. It is also possible that a pilot study will over or under estimate differences and we have therefore chosen conservative effect estimates for this multi-centre study.

With 1000 patients per group for analysis, the study will have 80% power at the 5% two-sided alpha level, to detect differences in the proportion of patients with clinician estimated blood loss >1000 ml of 15% vs. 10.7%, or 10% vs. 6.4%, equivalent to odds ratios of 0.62 and 0.68 respectively.

For the co-primary outcome of calculated blood loss, and estimated incidence in the control group of 14%, n = 1000 per group has 80% power to detect a difference 4.2%, equivalent to odds ratio of 0.67.

Based on the hospital statistics in the Dublin Maternity units for 2004 we estimate that there will be approximately 2500 elective caesarean sections at term each year between the five centres. Over the course of 30 months we would aim to recruit 2112 patients representing almost 34% of the available population (2112/6250) – this conservative estimate takes account of eligibility criteria and non-English speaking women. The sample size is slightly inflated from 2000 to allow for missing outcome data (full blood count not taken at the correct time or blood loss not measured).

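### Covariates beyond the stratification factors enter only through observed baseline imbalance, so the plan forgoes a free gain in precision (haemoglobin and haematocrit change) and possibly in power (calculated major haemorrhage)

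*Protocol article*

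**What the plan says.** The Statistical analysis section of the protocol article specifies intention-to-treat comparisons by logistic or linear regression, adjusted for the stratification variables. Recruitment and allocation (text under Exclusion criteria) gives these as centre and previous caesarean section. Other adjustment covariates can enter in one way only: "Secondary analyses will investigate the effects of further adjustment for any variables displaying marked imbalance between the arms at baseline". Secondary outcomes follow the same approach.

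Two sets of outcomes contain baseline measurements by definition:

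- Under Secondary outcomes, one objective is "to compare the objective change in haemoglobin and haematocrit before and 48 hours after delivery between the two groups".
- Under Outcome measures, major haemorrhage is a loss of at least 1000 ml calculated from pre- and post-operative haematocrit and a blood volume: "Where EBV estimated blood volume = Booking weight in kg × 85".

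Booking weight and pre-operative haematocrit or haemoglobin are not named as covariates in any model.

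**The concern.** Under randomisation, a baseline imbalance is a chance event, and its size says nothing about whether the variable predicts blood loss. A rule based on imbalance can admit an irrelevant variable and leave out a strong predictor that happens to be balanced. The text gives no threshold for how large an imbalance must be, so the secondary model cannot be written down before the data are seen.

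Meanwhile, variables that predict these outcomes by construction are already needed to compute them. A fixed 1000 ml cut-off applied to a loss that scales with booking weight is reached more easily by heavier women. A change score is correlated with its own starting value unless the pre/post regression slope is exactly 1. What is at stake is efficiency: wider intervals than necessary for the change outcomes, and possibly some power on one of the two primary outcomes.

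**Working it through.** **1. Does the stated power depend on these covariates?** The Sample size section says "With 1000 patients per group for analysis, the study will have 80% power at the 5% two-sided alpha level", for "15% vs. 10.7%, or 10% vs. 6.4%, equivalent to odds ratios of 0.62 and 0.68 respectively". For calculated loss it takes an "estimated incidence in the control group of 14"% and says "n = 1000 per group has 80% power to detect a difference 4.2%, equivalent to odds ratio of 0.67", that is 14% against 9.8%. The check is a two-proportion test with no covariates:

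power = Φ{ [ |p1 − p2| − c − 1.96·√(2p̄(1−p̄)/n) ] / √([p1(1−p1)+p2(1−p2)]/n) }, with n = 1000 and c = 0, or c = 1/n for a continuity correction.

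For 14% vs 9.8% with correction: (0.042 − 0.001 − 0.0284)/0.01445 = 0.873, which gives a power of 80.9%.

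| Rates | Power, c = 0 | Power, c = 1/n | n per group for 80%, corrected |
|---|---|---|---|
| 15% vs 10.7% | 82.0% | 80.2% | 996 |
| 10% vs 6.4% | 83.5% | 81.4% | 966 |
| 14% vs 9.8% | 82.7% | 80.9% | 979 |

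The stated 80% reproduces without any covariate gain. (The two odds ratios for clinician-estimated loss are printed in swapped order: 15% vs 10.7% gives 0.68 and 10% vs 6.4% gives 0.62. This does not affect the present point.)

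**2. Change in haemoglobin and haematocrit (linear model).** Let s² be the variance of the pre- and post-operative values (assumed equal) and r their correlation (not in the documents).

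- Raw change: 2(1−r)s².
- Adjusted for the pre-operative value: (1−r²)s².
- Ratio: (1−r)(1+r) / [2(1−r)] = (1+r)/2.

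| r (assumed) | Ratio | Variance reduction |
|---|---|---|
| 0.3 | 0.65 | 35% |
| 0.5 | 0.75 | 25% |
| 0.7 | 0.85 | 15% |
| 0.8 | 0.90 | 10% |

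**3. Major haemorrhage: why weight predicts it.** The loss equation is not visible in the text at hand. Assume loss = fractional haematocrit fall × blood volume, with blood volume = 85 × weight in kg. The fall needed to reach 1000 ml is then 1000/(85W):

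- 50 kg: 1000/4250 = 23.5%
- 70 kg: 1000/5950 = 16.8%
- 100 kg: 1000/8500 = 11.8%

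**4. Major haemorrhage: size of the power gain.** Trials of 1000 per group were simulated from this assumed formula, 1000 per scenario, with marginal rates fixed at 14% and 9.8%. Logistic regression was run without covariates and then with booking weight and pre-operative haematocrit. Mean weight was 70 kg and pre-operative haematocrit had mean 36 and SD 3. All distributional inputs are assumptions.

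| Weight CV | Slope of fall on pre-operative haematocrit | SD of fractional fall | Unadjusted | Adjusted | Gain (points) |
|---|---|---|---|---|---|
| 0.15 | 0 | 0.06 | 83.6% | 85.8% | 2.2 |
| 0.15 | 0 | 0.08 | 84.2% | 84.0% | −0.2 |
| 0.15 | 0.5 | 0.06 | 82.3% | 90.2% | 7.9 |
| 0.15 | 0.5 | 0.08 | 80.7% | 85.1% | 4.4 |
| 0.20 | 0 | 0.06 | 81.4% | 86.2% | 4.8 |
| 0.20 | 0 | 0.08 | 83.8% | 85.8% | 2.0 |
| 0.20 | 0.5 | 0.06 | 84.4% | 91.7% | 7.3 |
| 0.20 | 0.5 | 0.08 | 84.2% | 88.7% | 4.5 |

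The simulation error of each power figure is about √(0.83 × 0.17/1000) = 1.2 points, so the range is best read as about 0 to 8 points.

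**5. Where the logistic gain comes from.** In a generic simulation with one covariate of odds ratio 2.7 per SD, the standard error of the log odds ratio rose from 0.1405 to 0.148, while the odds ratio moved from 0.667 to a conditional 0.638. The signal ratio goes from |ln 0.667|/0.1405 = 2.88 to |ln 0.638|/0.148 = 3.04. Power rises because the estimand moves away from 1, not because the standard error shrinks.

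**The case against.** The strongest reply is that nothing here is wrong. The primary model is fixed in advance and includes the stratification factors, and randomisation keeps the comparison valid. The imbalance rule governs only secondary analyses placed beside that model. All of this stands. A reader might infer that the data choose the model used for the main inference, or that the trial is underpowered for want of these covariates. The text supports neither reading: the primary covariates are named, and step 1 shows no shortfall.

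A reader might also infer that precision is lost on every outcome. That is too strong. For the binary haemorrhage outcome the standard error does not fall with adjustment. Additional uterotonic use, the other primary outcome, contains neither haematocrit nor weight, and the same is true of transfusion, side effects and length of stay.

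It can be said that adjustment of a change score for its baseline is a detail for an unseen analysis plan. In part this is fair, since the article does not expressly exclude the baseline value. But it does state a covariate scheme and extends it to the secondary outcomes, so a plan that follows it would omit the baseline unless it happened to look imbalanced.

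Finally, the covariates may be incomplete. The Sample size section does expect missing data: "The sample size is slightly inflated from 2000 to allow for missing outcome data". However, a woman without booking weight or pre-operative haematocrit has no calculated loss, and one without a pre-operative value has no change score. Adjusting therefore removes nobody whose outcome can be computed.

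**Conclusion.** The point holds as a forgone gain, worth taking because it is free. The planned primary analysis is valid and meets its stated power.

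- **Change in haemoglobin and haematocrit:** variance about 10% to 35% lower with the pre-operative value added, for assumed r of 0.8 to 0.3 and equal variances. These are secondary outcomes on which the trial was not sized.
- **Calculated major haemorrhage:** about 0 to 8 points of power, resting on the assumed loss formula, weight spread, spread of haematocrit fall and slope on pre-operative haematocrit. The documents give none of these, so the size cannot be fixed more closely. The adjusted odds ratio is conditional on the added covariates and must be reported as such.
- **The imbalance trigger:** a poor selection rule that is written into the text, with its effect confined to secondary analyses.

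**What to change.** In the Statistical analysis section:

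1. For major haemorrhage by calculated blood loss, prespecify centre, previous caesarean section, booking weight and pre-operative haematocrit, and state that the odds ratio is conditional on them.
2. For change in haemoglobin and in haematocrit, prespecify centre, previous caesarean section and the pre-operative value of the same measure.
3. Replace the imbalance-triggered secondary adjustment with covariates named in advance for their expected prognostic value.

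The cost is wording only. The variables are already required to compute these outcomes, and neither the sample size nor data collection changes. The change should be made before unblinded outcome data are seen.
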